## Sample size (with justification):

### **Sample size calculation**

Sample size for baseline survey is calculated for 95% confidence interval ( $z=1.96$ ), based on the following assumptions: margin of error ( $\alpha$ ) =5%, estimated prevalence of diabetes= 9.5% (16), design effect=2 and anticipated response rate=80 %. We are only including age group  $\geq 25$  years, so we will have 4 age groups namely 25-34 years, 35-44 years, 45-54 years, 55-64 years for each sex (total strata=8). This will result in a sample size=2643. Sample size is calculated based on the method suggested by the WHO STEPWISE Approach(17). According to the STEPS sample size calculator, the margin of error of 0.05 is suggested in a baseline survey for the expected prevalence of 10% or greater. In addition, a smaller margin of error of 0.02 or 0.01 is considered appropriate when the expected prevalence is lower than 10%. In this study, the anticipated prevalence was 9.5%, which is very close to 10% and this being an assumption, the margin of error of 0.05 was included.

### **Sample size calculation for diabetic populations**

A lifestyle intervention study in a primary health care setting showed a mean reduction in fasting plasma glucose level by greater than 1 mmol/L after one year intervention in the diabetic population (18). Based on the standard deviation of mean reduction of fasting plasma glucose in the intervention arm of 2.1 (18), considering intraclass correlation of 0.01 and the design effect of 1.1 and 80% power into consideration, we will need 7 clusters with 11 individuals per intervention arm. To allow for the predicted dropout rate of 30%, the sample size was increased to 16 in each group i.e. 112 individuals per intervention group and the total sample size of the study will be 224.

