## 14. Introduction:

### 14.1 Background of Study (maximum 500 words):

While communicable diseases remain an important public health issue in developing countries, the rising burden of non-communicable diseases and their risk factors are rapidly rising too, posing a double burden on health systems. Diabetes is increasingly becoming a significant public health problem worldwide, leading to high morbidity and mortality resulting from clinically severe complications. The global prevalence of diabetes in 2010 was estimated to be around 6.4%, affecting 285 million adults, and is expected to increase to 7.7% by 2030. With ageing, the prevalence of diabetes is expected to increase by 69% in low-and middle-income countries (1). In particular, type 2 diabetes is becoming more widespread globally, accounting for over 90% of all diabetes cases (2). The rising prevalence is attributed to various modifiable risk factors such as changes in nutrition and life styles leading to physical inactivity and obesity as well as non-modifiable risk factors including family history and age related factors (3). Type 2 diabetes has reached epidemic proportions in South-East Asia Region, leading to significant increases in morbidity and mortality in recent years(4). Indeed, we noted in our previous systematic review and meta-analysis that type 2 diabetes is emerging as a major health care problem in Nepal, with a prevalence rate of 8.4% (5). There is also paucity of data on type 2 diabetes prevalence and available studies are not consistent with in their data collection methods regarding type 2 diabetes and related modifiable risk factors (6). Hence a study of such nature will help us to understand the problem and to design an appropriate intervention for diabetes management at the community level.

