**Study Population (Specify):**

The study population is diabetes patients who will be identified by screening.

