## Sampling Methods / Techniques (Specify)

The COBIN project has a population framework of all eligible participants prepared from the Voter List of the Election Commission. A systematic random sampling will be conducted to select participants in the baseline survey. If there is more than one participant from the same household eligible to participate in the study at the time of data collection, the *Kish* method will be adopted to select the participant. The same method will be applied for recruiting participants in the intervention phase.

The Lekhnath Municipality has 15 administrative units called wards (clusters). Out of 15 such wards, 1 ward was excluded by using simple random sampling before the randomization. Randomization was done for the clusters dividing 7 as intervention and 7 as control. After that, respondents who participated in the baseline survey will be the participants of the study.

Data will be collected by specially trained research assistants with a health professional background. Data about sociodemographic factors, lifestyle and prior illness will be collected by interviewing participants using STEPS questionnaires. Anthropometric data (weight, height, waist circumference) and blood pressure will be measured by the trained research assistants with a health professional background, height by a flexible non-stretchable measuring tape, weight by digital weighing machine, waist circumference by centimeter scale and blood pressure by digital sphygmomanometer.

Fasting blood glucose for the participants will be estimated by using a standardized digital glucometer (Infopia Co., Korea), using the capillary finger prick method. On a pre-informed date, fasting blood glucose estimation will be done. (Fasting being defined as no caloric intake for at least eight hours). Participants will be reminded by telephone for fasting glucose testing a day before the test. A person will be considered to be having diabetes if he/she will have fasting capillary blood glucose  $\geq 7.0$  mmol/l.

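### On the plan's own assumptions the baseline survey is expected to yield about 201 people with diabetes, not the 224 the trial is sized on, and power is about 77% rather than 80%

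*Protocol*

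**What the plan says.** Section 15 of the protocol holds two separate sample size calculations.

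- **Survey** (Sample size calculation). The inputs are "estimated prevalence of diabetes= 9.5% (16), design effect=2 and anticipated response rate=80" per cent, z = 1.96, a margin of error of 0.05 and eight age-by-sex strata. The conclusion is: "This will result in a sample size=2643".
- **Trial** (Sample size calculation for diabetic populations). A reduction of 1 mmol/L, SD 2.1, ICC 0.01, design effect 1.1 and 80% power lead to 7 clusters of 11 per arm. For 30% dropout this is raised to 16 per cluster: "112 individuals per intervention group and the total sample size of the study will be 224". The Proposal Summary (section 13) repeats 112 per arm.

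The link between the two is in the text on population and sampling. Under Study Population: "The study population is diabetes patients who will be identified by screening". Under Sampling Methods / Techniques, after randomisation of the wards, "respondents who participated in the baseline survey will be the participants of the study". The same section adds that the sampling method will also serve for recruitment in the intervention phase, without a number or a procedure. Section 22 gives 2643 as the number of participants required for the research.

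The Background (section 14.1) describes type 2 diabetes in Nepal "with a prevalence rate of 8.4% (5").

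**The concern.** If trial participants are the survey respondents found to have diabetes, the size of the survey fixes the size of the trial. The survey was sized to estimate prevalence, and the trial to detect a difference in fasting glucose. Nowhere does the protocol check that the first supplies the second. Should it fall short, the trial misses its stated enrolment before any dropout, and the 80% power attached to 224 is not what the design is expected to deliver.

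**Working it through.** **1. Reproduce the trial figure.** Difference 1, SD 2.1, two-sided 5%, 80% power:

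- 2 × (2.1 × (1.960 + 0.842))² = 69.2, so 70 per arm.
- 70 × 1.1 = 77 = 7 × 11.
- 11 / 0.70 = 15.7, so 16 per ward; 7 × 16 = 112 per arm and 224 in total.

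The stated figure reproduces exactly. Power at 77 evaluable per arm is 80.4%.

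**2. Reproduce the survey figure.**

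- 1.96² × 0.095 × 0.905 / 0.05² = 132.1.
- 132.1 × 2 (design effect) × 8 (strata) = 2113.8.
- 2113.8 / 0.80 = 2642.3, against the stated 2643.

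The figure reproduces only after division by the response rate. So 2643 is the number approached, and about 2,114 is the number expected to respond.

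**3. Expected yield for the trial.**

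- 2643 × 0.80 = 2114.4 respondents.
- 2114.4 × 0.095 = 200.9 people with diabetes, or 100.4 per arm and 200.9 / 14 = 14.3 per ward.
- 224 − 201 = 23 short, about 10%.

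**4. Could chance close the gap?** Normal approximation with continuity correction:

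- Simple binomial: SD = √(2114.4 × 0.095 × 0.905) = 13.5; (223.5 − 200.9) / 13.5 = 1.68; probability about 5%.
- Variance doubled for the survey design effect of 2: SD = 19.1; (223.5 − 200.9) / 19.1 = 1.19; probability about 12%.

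**5. Power after the planned dropout.**

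- 200.9 × 0.70 = 140.6 completers, that is 70.3 per arm and 10.04 per ward, against 154, 77 and 11.
- Design effect 1 + (10.04 − 1) × 0.01 = 1.09; effective n per arm = 70.3 / 1.09 = 64.5.
- 1 / (2.1 × √(2 / 64.5)) = 2.70; 2.70 − 1.96 = 0.74; power 77.1%. With the design effect held at 1.1 it is 76.8%.

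**6. Sensitivity to prevalence.** At 8.4%: 2114.4 × 0.084 = 177.6 people; × 0.70 = 124.3 completers, or 8.9 per ward; power about 72%.

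**7. What 224 would require.** Any one of these, with the other inputs unchanged:

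| Quantity | Needed | Assumed |
|---|---|---|
| Respondents (224 / 0.095) | about 2,358 | about 2,114 |
| People approached (224 / 0.095 / 0.80) | about 2,948 | 2643 |
| Prevalence (224 / 2114.4) | 10.6% | 9.5% |
| Response rate (224 / (2643 × 0.095)) | 89% | 80% |

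**The case against.** The case against making much of this is fair in several respects.

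- **The loss is small and depends on assumptions.** By the plan's own method power falls by about 3 points. The required 154 completers would still be reached if dropout were about 23% (1 − 154 / 200.9), and an effect of about 1.04 mmol/L (2.80 / 2.70) would restore 80%. The cited study reported a reduction of more than 1. All this stands. It means that the plan could be rescued by better luck than it assumes, not that its figures agree.
- **Further recruitment may be intended.** Sampling Methods mentions recruiting in the intervention phase, and Potential Biases speaks of recruiting after allocation. Neither gives a number or a procedure, and section 22 declares no pool beyond 2643. The possibility is open, but the gap is not closed.
- **2643 might mean completed respondents.** The yield would then be 2643 × 0.095 = 251 and there would be no shortfall. The plan's own formula contradicts that reading, because it has already divided by 0.80.

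Some stronger conclusions that a reader might draw are not supported:

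- *That the survey cannot supply 224.* The 201 is an expected value resting on an assumed prevalence, and 224 remains possible.
- *That only 14/15 of the yield is usable because one ward was dropped.* The protocol places the survey in the intervention and control clusters, which are the 14 randomised wards.
- *That 8.4% contradicts the plan.* It is a national background figure. The plan takes 9.5% from a survey of a semi-urban Nepali population, and the site is described as semi-urban. So 8.4% serves only as a sensitivity value.
- *That every ward must reach 16.* Sixteen is a planning average obtained by rounding up 11 / 0.70. Ward counts would vary around it even in a survey of ample size.
- *That power is really 70%.* A t reference with 12 degrees of freedom gives that figure, but it gives only 73% at the plan's own 11 per ward. Most of that gap from 80% is a separate matter.
- *That the shortfall would surface too late.* The work plan lists the survey and its analysis ahead of volunteer training and the intervention, so it should be seen before treatment starts.

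**Conclusion.** The point holds as an inconsistency between two stated calculations. Each is sound taken alone, but the survey as sized is not expected to supply the trial as sized: about 201 people with diabetes against 224, and about 10 per ward at follow-up against 11. Power is about 77% against the stated 80%. This rests on the plan's own 80% response, 9.5% prevalence and 30% dropout, on participants coming from the survey respondents, and on every respondent found to have diabetes enrolling. The last assumption favours the plan. The size is modest, so this should be corrected but does not undermine the design.

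**What to change.** In section 15, Sample size calculation for diabetic populations, and in the Proposal Summary, restate:

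- expected enrolment of about 200, about 100 per arm;
- an expected mean of about 14 per ward in place of a fixed 16, and about 10 per ward at follow-up;
- power of about 77% by the plan's method;
- as a sensitivity value, the 8.4% case: about 178 people and about 72% power.

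Beside this, note that 224 would need about 2,358 respondents, or about 2,948 approached, at 9.5%. If the sponsor prefers to keep 224, that means about 305 more people approached (2,948 − 2,643), and the figure in section 22 would change too. If recruitment in the intervention phase is meant to add participants, its number and procedure should be stated.

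Restating costs a few lines of text and a less favourable stated size and power. Enlarging the survey costs fieldwork.

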### Data Collection Technique / Methods (Specify):

The baseline survey will be performed in both the intervention and wait-list control clusters. The survey tool will be adopted from the WHO STEPWISE Package, which includes physical measurement (height, weight), socio-demographic information (age, sex, family size, occupation, income, and education), and life style factors (current exposure to tobacco and alcohol, diet and physical activity). Participants will be asked to provide a written consent to have measured via a finger stick blood sample and Glucometer.

The record of FCHV visit will be maintained by a supervisor. The same methodology will be used to conduct the follow-up survey after one year in both intervention and wait-list control clusters.

### Data Collection Tools: (please attached in annex)

Questionnaires

### Pre-testing the Data Collection Tools (if applicable):

Pre-testing of data collection tools will be conducted in the Lekhnath Municipality

### Validity and Reliability of the Study Tools:

WHO Stepwise Survey tool will be taken as a reference material for baseline and follow-up survey which will be adopted from Nepal Health Research Council's survey tool. The training materials will be developed based on the already available materials from WHO and other similar organizations.

## Potential Biases (if applicable):

There may be possibility of a selection bias in this study due to high loss to follow-up or failure to use intention to treat analysis. Moreover, selection bias can also be introduced through participant recruitment as our study will recruit participants after the clusters have been randomly allocated.

In the same way recruitment bias could occur in this study due to poor allocation concealment. If the allocation could not be concealed from the people doing the recruiting, there may be danger of recruitment bias.

Another important bias that could occur is the contamination bias. For instance, the subjects in the control group can be inadvertently exposed to the intervention group.

However, the risk of contamination will be minimized by randomization at the level of clusters. In order to reduce the possibility of contamination, we also have plans to collect every possible means of contamination between intervention and wait-list control participants during the follow-up survey, and, if these are found to be significant, we will make adjustments while estimating the effect.

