#### 13. Proposal Summary (maximum 500 words):

**Background:** Type 2 diabetes is one of the fastest growing chronic diseases worldwide. Despite its growing burden there is a lack of population approaches to reducing blood sugar among persons with diabetes, especially in developing countries. The health complications associated with type 2 diabetes can be prevented, delayed, or improved via early diagnosis and effective management. This research aims to examine the impact of a family-based home health education intervention on type 2 diabetes provided by Female Community Health Volunteers (FCHVs) at Lekhnath Municipality of Nepal.

**Method/design:** This is a community-based, open-masked, two-armed, cluster-randomized controlled trial with 7 randomly selected intervention and 7 wait-list control sites in Lekhnath Municipality of Nepal. A total of 112 subjects with type 2 diabetes will be recruited from the intervention sites and 112 subjects from the wait-list control sites. A 12-month family-based life style intervention will be administered through the help of FCHVs based on the Health Belief Model framework. Wards in the wait-list control will continue to manage their poor glycemic condition as usual and their intervention will be delayed for 12 months. Participants will be measured at baseline and 12 months later. The primary outcome is measures of glycemic control mean fasting blood glucose levels. Secondary outcome measures of the study include body mass index, blood pressure, alcohol use, tobacco use, diet intake, knowledge, quality of life, depression scores, physical activity, social support, and sedentary behaviors.

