The baseline survey will be performed in both the intervention and wait-list control clusters. The survey tool will be adopted from the WHO STEPWISE Package, which includes physical measurement (height, weight), socio-demographic information (age, sex, family size, occupation, income, and education), and life style factors (current exposure to tobacco and alcohol, diet and physical activity). Participants will be asked to provide a written consent to have measured via a finger stick blood sample and Glucometer. The record of FCHV visit will be maintained by a supervisor. The same methodology will be used to conduct the follow-up survey after one year in both intervention and wait-list control clusters. Knowledge and skills of FCHVs will also be assessed.

317

318

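### Wards are allocated before participants are surveyed, screened and consented in an open trial, and no concealment of the allocation from recruiters or residents is described

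*Protocol*

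**What the plan says.** Section 15, Sampling Methods / Techniques, reports the allocation in the past tense: "Randomization was done for the clusters dividing 7 as intervention and 7 as control". The next sentence is "After that, respondents who participated in the baseline survey will be the participants of the study". The survey itself lies in the future and takes place in wards that already carry an arm label: "The baseline survey will be performed in both the intervention and wait-list control clusters". Written consent for the finger-stick test belongs to that survey. Cases are found the same way, since "The study population is diabetes patients who will be identified by screening".

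The Proposal Summary (section 13) describes the masking: "This is a community-based, open-masked, two-armed, cluster-randomized controlled trial". On who does the fieldwork, Sampling Methods / Techniques says "Data will be collected by specially trained research assistants with a health professional background".

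Potential Biases states the consequence of the order, "selection bias can also be introduced through participant recruitment as our study will recruit participants after the clusters have been randomly allocated", and adds a conditional warning: "If the allocation could not be concealed from the people doing the recruiting, there may be danger of recruitment bias". The countermeasures that follow in that section deal with contamination only. Section 17 plans to adjust the analysis for baseline differences between arms if randomisation leaves any.

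**The concern.** In a cluster trial, randomisation protects the comparison of wards. It protects the comparison of participants only if entry to the study does not depend on the arm. Here every step that decides entry comes after allocation: answering the survey, fasting and attending for the test, and consenting. If field staff or residents know which wards get the programme now and which wait 12 months, any of these steps can go differently in the two arms. Section 22 gives residents a reason to behave differently, because it lists the participant benefits for the intervention areas only.

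The primary outcome is mean fasting glucose among those enrolled. An arm difference in who enrols would add directly to the estimated effect. A larger sample would not reduce it.

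**Working it through.** **1. Order of events.** The sentence that follows the randomisation statement could be read as saying that the survey had already been done. Two things rule that out: the survey is described in the future tense in wards already labelled by arm, and Potential Biases says outright that recruitment follows allocation. The order is therefore established.

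**2. What is already protected.** From Sampling Methods / Techniques:
- Who is approached: systematic random sampling from a voter-list frame, and the Kish method within households.
- Who is classed as diabetic: fasting capillary glucose of at least 7.0 mmol/l, read from a digital glucometer.

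Not protected: who responds, who attends fasting, who consents, and how hard non-responders are pursued.

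**3. Room for differential participation.** The baseline survey size reproduces: 1.96² × 0.095 × 0.905 / 0.05² = 132.1, and 132.1 × 2 × 8 / 0.80 ≈ 2642, against 2643 stated. At the anticipated 80% response, 0.20 × 2643 ≈ 529 people do not take part. The 80% is for the general survey; the protocol gives no rate for people with diabetes.

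**4. The plan's trial size.** With a difference of 1 mmol/L, SD 2.1, two-sided 5% and 80% power, n = 2 × (1.960 + 0.842)² × 2.1² / 1² ≈ 69.2, rounded up to 70 per arm. The design effect is 1 + (11 − 1) × 0.01 = 1.1, so 70 × 1.1 = 77 = 7 × 11. For 30% dropout, 11 / 0.70 = 15.7, rounded up to 16. Then 7 × 16 = 112 per arm and 224 in total, as stated. Holding back the allocation changes none of these.

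**5. Illustrative size of the bias.** The documents give no figure, so both inputs are assumptions. Let participation be p₁ in intervention wards and p₀ in control wards, and let the extra intervention enrollees have 12-month glucose lower by g than the rest. Then bias = (p₁ − p₀) / p₁ × g.

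| Participation (assumed) | g = 0.5 mmol/L | g = 1.5 mmol/L |
|---|---|---|
| 82% / 78% | 4/82 × 0.5 = 0.02 | 4/82 × 1.5 = 0.07 |
| 85% / 75% | 10/85 × 0.5 = 0.06 | 10/85 × 1.5 = 0.18 |

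Against the 1 mmol/L target this is about 2% to 18%.

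**6. Effect on the test.** With 77 analysed per arm, SE = 2.1 × √(2 × 1.1 / 77) = 0.355 mmol/L. With no true effect, a shift of 0.02 leaves the two-sided type I error at about 5% and a shift of 0.18 raises it to about 8% (normal approximation). A t reference with 12 degrees of freedom gives much the same: 5.8% at 0.1 and 10.0% at 0.25, against 5.9% and 10.8% under the normal.

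**The case against.** The strongest reply is that the protocol nowhere says the recruiters know the allocation. Its warning is conditional, the open label describes the trial as a whole, and data are collected by research assistants while the FCHVs deliver the programme. That stands. A reader might infer that unmasked staff recruit the participants, but the documents support only that no concealment from them is described.

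The second reply is that safeguards exist. Recruiters do not choose whom to approach and have little latitude over the diabetes classification, and control wards are promised the programme after 12 months, which may weaken the incentive to participate differently. This also stands, and it narrows the risk to response, fasting attendance, consent and contact effort. It does not remove it.

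Third, baseline glucose is measured and section 17 plans adjustment. Any part of the gap in step 5 that is already present at baseline would shrink under that adjustment or an analysis of change. Unmeasured differences, such as motivation, would remain.

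A reader might also take the work plan as proof that allocation could wait, because it lists the baseline survey before FCHV training. Its month shading is not legible in the text at hand, and row order alone is not a timeline. The better support is the statement in Sampling Methods / Techniques that FCHVs are trained after randomisation, although that does not date randomisation relative to baseline.

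**Conclusion.** The point holds in a limited form. The order (allocation, then survey, screening and consent) and the acknowledged risk are in the text. So is the gap: no concealment procedure is described, and the only analytic remedy is adjustment for observed differences. What is shown is a possible bias, not an actual one. Nor do the documents show that the allocation was disclosed to recruiters.

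The size is unknown. The range of about 0.02 to 0.18 mmol/L rests wholly on the assumed participation and outcome gaps, and so does its direction. The upper figure is one end of that range and should not be quoted as the expected bias. At the lower end the effect on the trial is negligible. The reason to act is that the protection costs no participants, while an unmeasured recruitment difference could not be repaired afterwards. Confidence is medium.

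**What to change.** In Sampling Methods / Techniques and in Potential Biases, state that the ward allocation is held by someone outside the field team. It should not be disclosed to research assistants, FCHVs or residents until survey, glucose screening, eligibility and consent are complete in all 14 wards. FCHV training then follows, which agrees with the existing statement that training comes after randomisation.

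Because randomisation is reported as done, the protocol should also say whether the result is already known in the field. If it is not, withholding it is enough. If it is, re-draw the allocation once, after the baseline data are locked, by an independent person and under a documented amendment that gives the reason, so that it cannot look like a choice between allocations. Balancing wards on number of cases and mean baseline glucose at that draw is optional.

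Cost: FCHV training waits until the slowest ward has finished baseline, and a re-draw needs an amendment and its paperwork. The sample size stays at 7 × 16 = 112 per arm. The change removes bias from allocation-dependent recruitment only. The selection bias from loss to follow-up, named in the same section, needs its own handling.

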## 17. Plan for Data Management and Analysis:

All analyses will be intention to treat, i.e., without regard to the compliance of individuals within their allocated study arm and with clustering-effect. At first, the baseline and follow-up characteristics will be compared to detect significant differences using appropriate tests such as student t-tests for normally distributed variables and chi-squared tests for categorical variables. As randomization will be at the ward (cluster) level in the study, random-effects model will be used to account for clustering effect. In addition, sensitivity of findings will also be tested by completing a per protocol analysis with the complete data set. In the event that randomization does not control for differences between the intervention and wait-list control cluster on baseline characteristics, we will statistically control for those differences in subsequent analysis of program effects. The final outcome will be modeled by using multiple linear regression analysis. All statistical analyses will be carried out in STATA, version 12. Two-sided p values will be reported with a statistical significance level of <0.05.

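### The protocol allows the effect estimate to be adjusted for contamination recorded at follow-up, with trigger and method undefined, which conflicts with its intention-to-treat rule

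*Protocol*

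**What the plan says.** Under Potential Biases (section 15), the protocol relies on randomising wards to limit contamination. It then plans to "collect every possible means of contamination between intervention and wait-list control participants during the follow-up survey" and adds: "if these are found to be significant, we will make adjustments while estimating the effect". It names no contamination measure, threshold or adjustment method, and does not say whether the adjusted result is primary, secondary or a sensitivity analysis. The same part also lists not analysing by intention to treat as a source of selection bias.

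Section 17 opens: "All analyses will be intention to treat, i.e., without regard to the compliance of individuals within their allocated study arm". It provides for one covariate adjustment, which applies "In the event that randomization does not control for differences between the intervention and wait-list control cluster on baseline characteristics". It labels one analysis as a sensitivity check: "sensitivity of findings will also be tested by completing a per protocol analysis with the complete data set". The final outcome is to be modelled by multiple linear regression, with random effects for wards. Contamination is not mentioned in section 17.

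**The concern.** Contamination here means exposure of control participants to the intervention. It arises after randomisation and is recorded a year later in an open trial. Intention to treat means that exposure actually received does not alter the comparison; an adjustment for contamination makes it do so.

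Two things are at stake. The first is which quantity the trial reports: the effect of allocating a ward to the programme, or the effect that would have been seen without contamination. The second is who decides and when. With an undefined trigger and no label, either estimate could become the headline once the data have been seen. The trial's single specific objective is the effect on blood glucose, so this ambiguity sits on the main result.

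**Working it through.** **1. The passages side by side**

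| Point | Potential Biases | Section 17 |
|---|---|---|
| Basis of comparison | Adjusted for contamination, conditionally | Allocation, regardless of compliance |
| Variables adjusted for | Contamination, recorded at follow-up | Baseline characteristics |
| Status of the adjusted result | None given | Only the per-protocol analysis is labelled as a sensitivity check |

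Nothing in the protocol reconciles the two columns.

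**2. What a covariate adjustment would estimate**

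Suppose contamination (yes/no, possible only in controls) enters a linear regression with allocation. The allocation coefficient is then exactly

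adjusted = mean(intervention) - mean(uncontaminated controls).

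With p the contaminated share of controls,

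adjusted - ITT = p × [mean(contaminated controls) - mean(uncontaminated controls)].

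The bracket is the effect of exposure plus any prognostic difference between the two kinds of control. The first part changes the estimand; the second is selection bias.

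**3. The plan's own figures**

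Inputs from the sample size section for the diabetic population: difference 1 mmol/L ("mean reduction in fasting plasma glucose level by greater than 1 mmol/L after one year intervention"), SD 2.1 ("standard deviation of mean reduction of fasting plasma glucose in the intervention arm of 2.1"), 80% power, ICC 0.01, 30% dropout. Section 17 gives two-sided 5%.

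- Per arm: 2 × (1.96 + 0.8416)² × 2.1² / 1² = 69.2, so 70 (power 80.4%).
- Design effect: 1 + (11 - 1) × 0.01 = 1.10; 70 × 1.10 = 77 = 7 × 11.
- Dropout: 11 / 0.7 = 15.7, so 16 per ward; 16 × 7 = 112 per arm, 224 in total.

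The stated sample size reproduces. It contains no contamination rate, so the size of the present problem cannot be derived from the protocol.

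**4. Illustration A: separating the two parts**

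Assumed, not in the protocol: logit of contamination among controls = -1.6 + U, with U a standard normal prognostic factor; y = 9 - 1.0 × (exposed) - 0.5U + N(0, SD 2); 2,000 per arm so that sampling error is small; 400 replicates.

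- Contaminated controls: 20.7%.
- ITT: -0.794, as expected from -1.0 × (1 - 0.207) = -0.793.
- Adjusted: -1.092. With allocation as instrument: -1.002.
- Total gap: 1.092 - 0.794 = 0.298. Change of estimand: 1.002 - 0.794 = 0.208. Selection bias: 1.092 - 1.002 = 0.090.
- With no true effect: ITT 0.00, adjusted -0.088.

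**5. Illustration B: planned evaluable size**

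7 + 7 wards of 11, SD 2.1, ICC 0.01, 4,000 runs per scenario, ordinary least squares. Assumed: 10%, 20% or 30% of controls contaminated, each receiving the full effect; contamination propensity correlated 0.7 with a prognostic factor whose correlation with outcome is r; trigger taken as p < 0.05 for the contamination term. Results at 20%:

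| True effect | r | ITT | Adjusted | Adjusted only if significant |
|---|---|---|---|---|
| -1 | 0 | -0.80 | -1.00 | -0.92 |
| -1 | 0.3 | -0.81 | -1.16 | -1.14 |
| -1 | 0.5 | -0.81 | -1.27 | -1.26 |
| 0 | 0 | 0.00 | -0.01 | 0.00 |
| 0 | 0.3 | 0.01 | -0.15 | -0.07 |
| 0 | 0.5 | -0.01 | -0.27 | -0.20 |

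Over all three contamination rates with no true effect and r above 0, the triggered estimate ran from -0.03 to -0.29 mmol/L. It rejected in 7.5% to 15.9% of runs, against 5.5% to 6.7% for allocation only; the model ignores the small ICC, so the latter is slightly above 5%. With r = 0 the triggered estimate was about 0.00 under the null. With a true effect of -1 and r = 0 it was -0.92, a mixture of the ITT effect (-0.80) and the uncontaminated effect (-1.00).

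**The case against.** The strongest reply is that the protocol never says how it would adjust. A covariate term is plausible because section 17 offers regression, but an instrumental-variable estimate is also an adjustment for contamination, and it respects randomisation. The method could properly be left to an analysis plan. This stands: bias cannot be asserted as a fact of the plan.

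A reader might also infer that the trigger is a significance test. No test, level or comparison is named at that point, and the word may simply mean substantial. Either way the decision depends on the data, so the criticism of an undefined trigger survives; the reading as a 5% test does not.

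A reader might further infer that motivated controls will seek out the programme and so create an apparent effect where there is none. The protocol's only example is inadvertent exposure. Inadvertent exposure may still be related to prognosis, but when it is not, Illustration B shows no spurious effect and the adjustment recovers the uncontaminated effect of -1.00.

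It is also tempting to quote the adjusted estimate in Illustration A as 38% larger than ITT (0.298 / 0.794). Most of that is the removal of dilution. The selection part, 0.09 mmol/L, is about a quarter of the planned standard error (2.1 × √(2/70) = 0.36).

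Finally, section 17 follows its all-analyses statement with a per-protocol analysis, so the statement is not literally exclusive, and ITT could be read as primary with contamination secondary. But the per-protocol analysis carries a sensitivity label and the contamination adjustment carries none.

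**Conclusion.** The point holds as a conflict within the protocol and a badly fixed rule. One part lets a variable measured after randomisation alter the effect estimate, on an undefined condition and with no supplementary label. Section 17 says analyses disregard compliance, and the protocol itself names departure from intention to treat as a source of bias. This does not depend on the adjustment method.

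The consequences do. If contamination enters the planned regression, the estimand always moves away from the effect of allocation. Selection bias is added only if contamination is related to prognosis. The sizes shown (a gap of about 0.30 mmol/L, of which about 0.21 is estimand and 0.09 selection; up to -0.29 under the null in the less favourable scenarios) rest on contamination rates and prognostic links that the protocol does not contain. They show direction and mechanism and do not predict this trial's result. The documents do not support a claim that the reported effect will be inflated.

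**What to change.** State in both Potential Biases and section 17 that the primary estimate compares wards as allocated, with no contamination term. Report contamination by arm descriptively. If an estimate adjusted for contamination is wanted, prespecify it as supplementary: define the contamination measure, name a method that respects randomisation (for example, allocation as instrument, with its assumptions stated and clustering accounted for), and produce it whatever the observed level of contamination, with no significance trigger.

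The cost is a few sentences and one optional analysis of data already planned. The sample size stays at 77 evaluable and 112 recruited per arm. The downside is that the primary effect will look smaller if contamination occurs, and the sample size makes no allowance for that dilution: in Illustration B a true effect of -1 becomes about -0.90, -0.80 or -0.70 mmol/L with 10%, 20% or 30% of controls contaminated.
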